#### Dietary Intake

To assess participant dietary intake including nutrients that may be associated with mental health and child development including iodine, selenium, and iron intake, participants were asked to complete a weighed 4-day diet diary within 2 weeks of the initial study visit. All 4 days were consecutive and included one weekend day. Each participant was requested to record food items, brands, amount consumed, and the content of the nutritional information panel if applicable. All food and beverage items consumed were weighed and measured with a QM-7288 electronic kitchen scale (Digitech), and household measurement cups and spoons were provided. The Digitech scale can weigh up to 5 kilograms with an accuracy to 1 gram; all women were shown how to use the scale to quantify food items. All participants received both written and oral instructions on how to complete the record, which included a written example of a 1-day food record. Women were also asked to include dietary supplements consumed. When eating or dining out, participants were asked to estimate the portion size of all food eaten. The food record and equipment were collected or return posted 2 weeks after the initial visit.

A 69-item self-administrated semiquantitative iodine- and selenium-specific food frequency questionnaire, adapted from an Australian study of pregnant women [42], was used to estimate habitual maternal iodine and selenium intake at the first and third study visits. An iron-specific food frequency questionnaire, validated by other female population groups in New Zealand, was used to assess women’s iron-related dietary patterns [43] at the second study visit. Within 2 weeks of this visit, participants also completed a 3-day estimated food dietary record for their infants to enable assessment of infant nutrient intakes at weaning periods.

All dietary data were entered into Foodworks 9 Professional (Xyris Pty Ltd) online and analyzed using data sets from the New Zealand Foodfiles 2016 to estimate nutrient intake. When food items were not included in Foodfiles 2016, new food items were created based on the information directly provided by participants (ie, food packages) or from appropriate international databases from Australia and the United States. Estimates for iodine concentrations of categories of bread (eg, white, fiber white, fruited, mixed grain) were based on data from the Ministry of Primary Industries [22], since iodine content has not been determined for all commercially made bread in New Zealand after the mandatory fortification of bread with iodized salt. It was difficult to quantify the amount of discretionary salt added to food. However, for women who reported using iodized salt, 48 µg of iodine (equivalent to 1 g of salt) was added to their iodine intakes [21]. Dietary supplements used by participants were entered into Foodworks as a new food item based on nutritional information obtained from the manufacturers. To ensure accuracy and completeness, a registered nutritionist (YJ) checked all dietary data and then transferred the data to SPSS Statistics (IBM Corporation) version 23 for statistical analysis.

#### Anthropometry

Maternal and infant anthropometry measurements were obtained at each study visit. Women’s weight was measured using the same annually calibrated weighing scale with a capacity of 150 kilograms (Detecto). Before standing on the scale, participants were asked to remove their shoes and to wear minimum clothes. Body weight was recorded to the nearest 0.1 kilogram. Height was measured by using a Toledo stadiometer and recorded to the nearest millimeter [44]. Maternal body composition was determined using both bioelectrical impedance analysis (InBody230, InBody Co) and air displacement plethysmography (BodPod, COSMED SRL). Measurements were completed under the following conditions: minimal clothing, wearing swimming cap, before midday, after urination, normal room temperature (20℃ to 25℃), with no exercise, eating, drinking, or bathing/showering within 2 hours prior to measurement (preferably completing the measurement after breastfeeding the baby). On the day of the test, quality control steps for BodPod were carried out by following the manufacturer’s instructions, with acceptance criteria being volume ±100 mL of actual volume and standard deviation ≤75 mL.

Infant recumbent length was measured crown to heel using an infant length board and recorded to the nearest millimeter. Infant weight (without clothing and diapers) was measured using a baby weighing scale (Nagata Scale Co Ltd) and recorded to the nearest 10 grams. Infant head circumference was measured over the most prominent part on the back of the head (occiput) and just above the eyebrows (supraorbital ridges) by using a flexible, nonstretch tape [44] and recorded to the nearest even millimeter.

#### Ultrasound Measurement of Thyroid Gland Volume

A portable ultrasound (uSmart 3200T Ultrasound System, Teratech Corp) equipped with a linear transducer (7 to 15 mHz) was used for the thyroid measurement. Women were examined in a supine position (an adequate neck extension was achieved by placing pillows under the shoulders). Longitudinal and transverse scans were performed. Measurements of anteroposterior diameter and width (mediolateral diameter) were obtained with electronic calipers on a transverse image. The maximum lobe length was measured on a longitudinal width. The total volume of each thyroid gland was the sum of the volumes of left and right lobes, excluding the volume of the isthmus but including any nodules and/or cystic areas. The formula used to calculate the volume for each lobe is anteroposterior diameter × width × length × 0.479 [45]. A total volume greater than 18 mL was defined as thyroid enlargement based on the normative thyroid volume in iodine sufficient populations [46]. Any participant with observed abnormalities was referred to clinical health professionals for further assessment.

#### Biomarker Analysis

During each study visit, spot urine samples from each participating woman and her infant were collected to assess iodine, selenium, and creatinine excretion. All maternal spot urine samples were collected in the morning and immediately frozen and stored at –20℃. Infant urine was collected using a 100 mL pediatric urine bag placed inside the diaper and checked every 10 minutes. The collected urine was frozen and stored at –20℃ for later analysis. Spot urine samples can be used to estimate iodine status of a population but not for individual iodine deficiency diagnosis [47]. It was not possible to estimate dietary iodine and selenium intake for lactating women via urine as we were unable to determine the daily loss of selenium from breast milk. As creatinine output is relatively constant, the adjusted iodine/creatinine ratio (µg iodine per g creatinine) can be used as a proxy measure of iodine excretion [48].

Lactating women were asked to provide a breast milk sample (approximately 30 to 50 mL) at each visit using an Allegro electric breast pump (Unimom NZ) if required. All breast milk samples were collected before noon on the study visit day, and timing of breast milk collection was not standardized. Breast milk samples were analyzed for iodine and selenium concentration, allowing for estimations of infant intake of iodine and selenium based on 750 mL/d of milk production [49].

Iodine and selenium concentration in both urine and breast milk samples were determined by an accredited commercial laboratory (Hill Laboratories) using inductively coupled plasma mass spectrometry (ICP-MS) [50]. Quality control procedures included analysis of blanks, analytical repeats, and certified reference material to ensure accuracy and precision. The Massey University Nutrition Laboratory measured creatinine using the Jaffe method in a Flexor E (Vital Scientific) biochemistry analyzer.

To assess further selenium status, toenail clippings from women and nail clippings from infants were collected. Toenail clippings have been used to determine selenium concentrations in large cohort or epidemiological studies, such as for the preeclampsia risk in pregnant women [51]. The instruction for sample collection was explained to participants during each study visit and nail clippings were self-collected by participating women at home, with the collected samples brought back by the participants at the following study visit. All toenail clippings were stored at room temperature prior to analysis. Nail clipping samples will be prepared by using the method adapted from nail zinc analysis [52]. This involves washing all nail clipping samples by using 5 minutes contact with 25 mL portions in the order of acetone, water, acetone, water, and water [53]. Selenium concentration will be measured by ICP-MS.

During the second study visit, to assess blood hemoglobin concentrations, the handheld HemoCue Hb 201+ device (HemoCue America) was used, a standard in hemoglobin point-of-care testing [35,54]. It requires a finger prick and wicking of capillary blood into a pretreated microcuvette for analysis. Quality tests using external, liquid controls were necessary for each day of instrument use prior to sample analysis.

A qualified and experienced phlebotomist collected nonfasting maternal venous blood samples (22 mL) at the second study visit. Samples were centrifuged and aliquoted into microcentrifuge tubes prelabeled with participant unique sample ID and then stored at –80℃. In conjunction with the hemoglobin results, collected maternal venous blood samples were used to determine iron status by measuring soluble transferrin receptors and serum ferritin (using the chemiluminescent microparticle immunoassay [CMIA] method), which reflects iron storage, but if serum ferritin levels are increased during infection or inflammation, it may mask any iron deficiency results [55]. Therefore, an inflammatory marker, C-reactive protein, was measured (tested by an immunoturbidometric method analyzed on an Abbott C Series analyzer [Abbott Labs]).

Venous blood samples were assayed for hormonal biomarkers: free T3, free T4, and thyroid stimulating hormone via CMIA method; thyroglobulin (Tg, Beckman Coulter Access method); and antithyroglobulin antibodies (anti-Tg, CMIA method) at Canterbury Health Laboratories. Serum thyroglobulin has been suggested as an alternative method to assess individual iodine status reflecting a period of months [56]; to avoid potential underestimation of thyroglobulin, anti-Tg and antithyroid peroxidase (anti-TPO) were measured. Selenium status was assessed by determining the biomarker plasma selenium via ICP-MS method [57].

Details of data and biological samples collected from both mothers and infants throughout the study period are summarized in Tables 1 and 2.

**Table 1 table1:** Summary of outcome measures collected from participating women and their infants.

Outcome		Visit 1	Visit 2	Visit 3

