**Methods:**

Breastfeeding women aged over 16 years with a healthy term singleton infant were recruited from Manawatu, New Zealand. Participants attended study visits 3, 6, and 12 months postpartum. Maternal questionnaires investigated supplement use before and after birth, iodine knowledge, and demographic information. Dietary assessment and urine, blood, and breast milk samples were taken to measure iodine, selenium, and iron intake/status. The Edinburgh Postnatal Depression Scale was used repeatedly to screen for postnatal depression. Thyroid hormones (free triiodothyronine, free thyroxine, thyroid stimulating hormone, thyroglobulin, antithyroglobulin antibodies, and antithyroid peroxidase) were measured in blood samples, and thyroid gland volume was measured by ultrasound at 6 months postpartum. Infant iodine and selenium concentrations were determined in urine. The Ages and Stages Questionnaire was used to assess infant development at 4, 8, and 12 months.

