### Outcome Measures

#### Questionnaires

At the initial visit, general baseline questions were asked about salt and supplements use, nutrition knowledge of iodine, tobacco and alcohol use, breastfeeding patterns, general health, and demographic information (including age, ethnicity, educational attainment, household size, and income). Potential changeable information including tobacco and alcohol use, breastfeeding patterns, and general health was also sought at the second and third visits.

Participants were assessed about their general health and that of their infants by online questionnaire when infants reached 6 months and 12 months of age. During the postpartum period, stress may negatively affect immunity, and the occurrence of infection symptoms can be an estimated measurement of postpartum immune function. The Carr Infection Symptom Checklist, which has been validated for use with postpartum women [38], was used to measure the symptoms of infection experienced by the mother since the birth. The Infant Symptom Checklist (which reports the frequency of symptoms of common illnesses in young infants) was used to measure the health of infants [38].

The 10-item EPDS was completed online by participating women to assess any symptoms of depression and anxiety over the previous 7 days. Women recorded severity of symptoms on a 4-point scale [39]. Specified anxiety disorders were evaluated using the EPDS-3A, a cluster of selected question items numbered 3, 4, and 5 from the original EPDS [40]. This is a validated tool to screen for probable anxiety and depression during the postpartum period. A cutoff point of 13 or above was used to define high levels of depressive symptoms [35]. Any woman whose score equaled 13 or above was advised to see her general practitioner for further evaluation as well as being provided with an information sheet containing postnatal depression services in New Zealand. Only study participants with the correct link supplied via emails could complete these questionnaires. All questions were answered in the same order. Participants could not go back to change their answers once the questionnaire was completed. Answers from incomplete questionnaires may be used for analysis.

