**Dietary intake**				
	Maternal 4-day dietary diary	x		
	Maternal food frequency questionnaire–iodine/selenium	x		x
	Maternal food frequency questionnaire–iron		x	
	Infant 3-day dietary diary		x	

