**Breast milk (if available)**									
	Iodine	x		x			x		
	Selenium	x		x			x		

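### A single milk volume of 750 mL/d, with no condition on age or feeding pattern, overstates milk-derived iodine and selenium intake in partly breastfed infants

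*Protocol article*

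**What the plan says.** The abstract gives the schedule: "Participants attended study visits 3, 6, and 12 months postpartum". Under Biomarker Analysis, "Lactating women were asked to provide a breast milk sample (approximately 30 to 50 mL) at each visit", and Table 2 lists milk iodine and selenium at all three visits where milk is available. The same paragraph of Biomarker Analysis says the results are used for "allowing for estimations of infant intake of iodine and selenium based on 750 mL/d of milk production". That is the only volume given, and nothing restricts it to a visit, an age or a feeding group.

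Other parts of the article show that feeding is expected to change:

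- Dietary Intake, on the second visit: "participants also completed a 3-day estimated food dietary record for their infants to enable assessment of infant nutrient intakes at weaning periods". Table 1 lists this item ("Infant 3-day dietary diary") at visit 2 only.
- Questionnaires: information regarded as liable to change, including "breastfeeding patterns, and general health was also sought at the second and third visits".
- Selection Criteria: women had to be breastfeeding at entry. Exclusive breastfeeding is not required.

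**The concern.** Intake from milk is concentration times volume. The study measures the first factor and fixes the second at one constant. A constant is a workable convention for fully breastfed infants. It is harder to defend in a cohort followed to 12 months, where the design anticipates weaning around visit 2 and asks again about breastfeeding at visits 2 and 3. A partly weaned 12-month-old would be credited with the same volume as a fully breastfed 3-month-old.

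Two things are at stake. Milk-derived intake would be too high in infants who take less than 750 mL/d, and by more in those who take least. A comparison across visits would also miss any change in intake that comes from a change in volume, which is the change weaning produces.

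**Working it through.** **Inputs.** Assumed volume 750 mL/d (Biomarker Analysis). Milk sampled at 3, 6 and 12 months (abstract; Biomarker Analysis; Table 2). Infant food record at visit 2 only (Table 1). True milk volume V is not given, so a range of 200 to 750 mL/d is assumed here. The concentration C used below to show absolute amounts, 100 µg/L iodine, is also an assumption. The 750 mL/d is itself an assumed constant taken from a cited source, so there is no computed figure to reproduce.

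**Step 1: milk-derived intake.** Estimated = C × 0.750 L/d. True = C × V/1000. The ratio is 750/V, whatever the concentration and for either mineral.

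| Assumed V (mL/d) | 750/V | Overstatement |
|---|---|---|
| 750 | 1.00 | 0% |
| 700 | 1.07 | 7% |
| 600 | 1.25 | 25% |
| 500 | 1.50 | 50% |
| 400 | 1.88 | 88% |
| 300 | 2.50 | 150% |
| 200 | 3.75 | 275% |

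At C = 100 µg/L the rule returns 75 µg/d of iodine for every infant. The true milk-derived amounts would be 60, 40 and 20 µg/d at 600, 400 and 200 mL/d.

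**Step 2: change between visits.** The ratio of estimated intakes at two visits is (C₂ × 0.750)/(C₁ × 0.750) = C₂/C₁. The true ratio is (C₂ × V₂)/(C₁ × V₁). The volume term is lost. If concentration stays constant and V falls from 750 to 400 mL/d, true milk-derived intake falls by (750 − 400)/750 = 47%, while the estimate shows no change.

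**Step 3: total intake.** Let F be iodine from food and formula. A milk-only estimate exceeds the true total only if C × 750/1000 > C × V/1000 + F, that is, if F < C × (750 − V)/1000. At C = 100 µg/L the break-even F is 15, 35 and 55 µg/d for V of 600, 400 and 200 mL/d. Below it the total is overstated; above it the total is understated. The documents do not give F, so the sign cannot be settled. If the visit 2 food record is added to milk fixed at 750 mL/d, and the record captures F correctly, the sum is too high by C × (750 − V)/1000, which is the same 15, 35 or 55 µg/d.

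**The case against.** The article does not say in so many words that the 750 mL/d estimate is made at 6 and 12 months or for partly weaned infants. It says the assays allow such estimates. A condensed article may leave to a fuller document which visits and infants a derived variable covers. This stands as a caution: use at all three visits is the plain reading, since the sampling sentence covers every visit and the volume follows without a qualifier, but it is still an inference. It does not remove the point, because the article states a specific number without conditions.

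The size is also open to challenge, since the documents contain no infant milk volumes. That is correct. The percentages follow from assumed values of V and do not measure the error in this cohort.

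Two stronger readings are tempting, and the documents support neither:

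- A reader might infer that infant intake as a whole is biased upward and that inadequate intake is under-counted. Adequacy depends on total intake, and step 3 shows that the sign of the error in the total is undetermined. Nor is food ignored throughout, since a food record exists for visit 2.
- A reader might infer differential bias in the link between infant nutrition and neurodevelopment. The infant objective concerns iodine and selenium status, measured in urine, and in nails for selenium. Statistical Analysis names no model that uses milk-derived intake. The concern would extend there only if this variable were later used as an exposure.

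A correction that scales volume by recorded feeding pattern would need a conversion from pattern to millilitres, and the article describes none. That objection is sound, so the fix below avoids it.

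**Conclusion.** The point holds for milk-derived intake. As written, one unconditional volume is attached to milk sampled at 3, 6 and 12 months, against the article's own expectation of weaning from about visit 2. For any infant taking less than 750 mL/d, milk-derived iodine and selenium intake is overstated by 750/V: 25%, 50% or 88% at assumed volumes of 600, 500 or 400 mL/d, and nothing at 750. A change across visits in the derived figure carries information on concentration only. This rests on reading the volume as applying at every visit and on assumed values of V.

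The scope is limited. Infant intake is not among the stated primary outcomes, and the estimate is a secondary descriptive quantity with no stated inferential role. The conclusion does not extend to total intake, to the prevalence of inadequate intake, or to the neurodevelopment analyses. The rule should still be corrected, because a 6- or 12-month intake figure produced by it could mislead and the correction is cheap.

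**What to change.** Revise the derivation in Biomarker Analysis as follows.

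- Apply 750 mL/d only to infants recorded as fully breastfed at the visit concerned, using the breastfeeding questions asked at all three visits.
- For partly breastfed infants at visits 2 and 3, report milk concentration, or report intake over a stated range of assumed volumes. Label the result as milk-derived.
- At visit 2, add iodine and selenium from the 3-day infant food record before making any statement on total intake, and carry the volume range through to the sum.
- At visit 3, where Table 1 lists no infant food record, make no statement on total intake.
- Do not interpret a change in estimated intake across visits as a change in infant intake where the volume was held constant.

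Data collection is complete and the inputs already exist, so the change is to wording and to one derived variable. The cost is that intake at 6 and 12 months is reported less precisely, as a range or as a concentration.

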**Dietary intake**				
	Maternal 4-day dietary diary	x		
	Maternal food frequency questionnaire–iodine/selenium	x		x
	Maternal food frequency questionnaire–iron		x	
	Infant 3-day dietary diary		x	
**Anthropometry**				
	Maternal weight and height	x	x	x
	Maternal body composition via BodPod and BIA^a^	x	x	x
	Infant weight, height, and head circumference	x	x	x
**Biochemistry**				
	Maternal spot urine samples	x	x	x
	Maternal breast milk samples	x	x	x
	Maternal toenail clipping samples	x	x	x
	Maternal venous blood samples		x	
	Maternal capillary blood samples		x	
	Infant spot urine samples	x	x	x
	Infant nail clipping samples	x	x	x
**Others**				
	Maternal thyroid gland volume via ultrasound		x	
	Maternal Edinburgh Postnatal Depression Scale results	x	x	x
	Maternal self-reported health questionnaire	x	x	x
	Maternal iodine nutritional knowledge questionnaire	x		
	Infant health questionnaire reported by mothers	x	x	x

^a^BIA: bioelectrical impedance analysis.

**Table 2 table2:** Analysis from biological data collected at each study visit for the Mother and Infant Nutrition Investigation study cohort.

Samples		Visit 1			Visit 2			Visit 3	
		Mothers	Infants	Mothers		Infants	Mothers		Infants
**Spot urine**									
	Iodine	x	x	x		x	x		x
	Selenium	x	x	x		x	x		x
	Creatinine	x		x			x		
**Breast milk (if available)**									
	Iodine	x		x			x		
	Selenium	x		x			x		
**Blood**									
	Iodine status^a^			x					
	Selenium status^b^			x					
	Iron status^c^			x					
	Thyroid function^d^			x					
